## Abstract

**Background:**

Alzheimer’s disease is characterised by a loss of cognitive function and behavioural problems as set out in the term “Behavioural and Psychological Symptoms of Dementia”. These behavioural symptoms have heavy consequences for the patients and their families.

A greater understanding of behavioural symptoms risk factors would allow better detection of those patients, a better understanding of crisis situations and better management of these patients. Some retrospective studies or simple observations suggested that personality could play a role in the occurrence of behavioural symptoms. Finally, performance in social cognition like facial recognition and perspective taking could be linked to certain personality traits and the subsequent risks of behavioural symptoms.

We propose to clarify this through a prospective, multicentre, multidisciplinary study.

*Main Objective:*

- To assess the effect of personality and life events on the risk of developing behavioural symptoms.

*Secondary Objectives:*

- To evaluate, at the time of inclusion, the connection between personality and performance in social cognition tests;

- To evaluate the correlation between performance in social cognition at inclusion and the risks of occurrence of behavioural symptoms;

- To evaluate the correlation between regional cerebral atrophy, using brain Magnetic Resonance Imaging at baseline, and the risk of behavioural symptoms.

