#### B. Secondary objectives

– To evaluate the relationship between premorbid personality and performance in social cognition testing,– To evaluate the relationship between performance in social cognition testing at study inclusion and the risk of developing BPSD,– To evaluate the relationship between the distribution of regional cerebral atrophy using 3D brain MRI at study inclusion, social cognition performance and the risk of developing BPSD.

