#### MRI

A morphologic MRI will be performed as part of the battery of exploratory tests usually carried out. Acquisition will be performed on a 1.5 Tesla systems. The examination will include a 3D T1-weighted sequence an axial T2 sequence an axial T2* sequence and an axial FLAIR sequence. Voxel Based Morphometry (VBM) procedures will be used to analyze brain volumes and to evaluate the correlation between the score obtained by subjects and the grey matter density on their anatomical MRI scans. The segmentation of 3D T1-weighted images will be performed using SPM2 software and the optimized VBM method described by Senjem et al. [52].

The different measure variables used in PACO study are summarized in Table 1.

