#### Data analysis

To assess each study objectives, univariate and then multivariate analyses will be done to take into account potential confusion factors:

To evaluate the link between personality (traits and disorders) and the onset of BPSD, exploratory analyses (e.g. PCA) correlation between personality type or disorder and type of BPSD will be used.

Logistic regression models will be used for binary variables obtained from the NPI-Q and the Apathy Inventory, and linear regression models for continuous explanatory variables: intensity of the behavioural problems and total NPI-Q score.

ANOVA with repeated measures and survival models will be used to study the occurrence of these BPSD over time as seen during the various visits.

Exploratory analyses will be done to define a patient’s typology. Then, correlation between personality type and performance on social cognition tests will be assessed using linear regression models.

The link between baseline performance on social cognition tests and the risk for the onset of BPSD will be assessed with logistic regression models and survival models.

Finally, correlation between the type of BPSD and the difference in distribution of regional cerebral atrophy observed with MRI will be done using specific statistical parametric mapping (SPM) software.

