In PACO study, we are expecting to find correlations between personality dimensions and the risk of being affected by BPSD. We hypothesize that high level of neuroticism and low level of conscientiousness will be more specifically associated with BPSD, in particular affective domains such as depression, anxiety and apathy. As cognitive decline could be positively or negatively influenced by personality, this potential association will be studied [59, 60]. Moreover, as personality development is considered to be influenced by environmental factors, childhood and adult life events will be collected to assess their possible influence on the course of AD. This would allow us, for example, to highlight the possible effects of previous exposure to a trauma or childhood deficiencies.

Subjects included in PACO study will perform a comprehensive social cognition battery including facial emotion recognition tasks. Several publications have highlighted that AD patients experience an increasing deficit in facial emotional expression recognition as the disease progresses [23], but little is known concerning the very early stage of AD [61]. Consequences of impaired facial emotion recognition on behavioral troubles in AD are questioned and should be clarified [62]. Thus, a secondary objective of the PACO study is to compare social cognition ability between MCI and mild AD, and to identify potential relationships between social cognition abilities and BPSD occurrence during the patient’s follow-up.

PACO project includes MRI 3D sequence at baseline. Different studies have linked impaired emotion recognition in psychiatric or neurologic disease to disturbances or damages of the fronto-temporal brain network [63–65]. Social cognition parameters could be correlated to initial regional cerebral volume and/or the atrophy observed one year later, which could itself be correlated to a higher risk of developing BPSD. For instance, some orbito-frontal atrophy may predict the occurrence of BPSD. Recent evidence suggests that personality traits may be related to neuroanatomical structures. Jackson et al. [66] found that higher neuroticism was associated with specific brain regions atrophy, whereas higher conscientiousness was related to larger regional volumes in healthy aging. It could be hypothesised that an interaction between personality dimension, regional brain atrophy, and BPSD may exist in AD.

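### The MRI objective concerns the risk of developing BPSD, but its one named analysis is a voxelwise correlation with BPSD type, not tied to new onset, so the objective is only partly answered

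*Protocol article*

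**What the plan says.** **Objective.** The abstract states it as "To evaluate the correlation between regional cerebral atrophy, using brain Magnetic Resonance Imaging at baseline, and the risk of behavioural symptoms". The Secondary objectives section of the protocol article asks how three things relate: "distribution of regional cerebral atrophy using 3D brain MRI at study inclusion, social cognition performance and the risk of developing BPSD". Table 1 classes the MRI atrophy measurement as an influencing factor, and also as a secondary outcome variable. The Discussion suggests, as an example, that "some orbito-frontal atrophy may predict the occurrence of BPSD". It also hopes that personality, social cognition and atrophy, assessed together, may help clinicians to recognise patients at higher risk.

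**MRI analysis.** The one sentence in Data analysis that names MRI reads, in part, "correlation between the type of BPSD and the difference in distribution of regional cerebral atrophy observed with MRI will be done using specific statistical parametric"; the tool is the SPM package. The MRI section adds that voxel-based morphometry (VBM) will be used to study brain volumes and "to evaluate the correlation between the score obtained by subjects and the grey matter density on their anatomical MRI scans". The score is not named.

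**Parallel objective.** For social cognition, the sentence just before the MRI sentence reads, in part, "baseline performance on social cognition tests and the risk for the onset of BPSD will be assessed with logistic regression models and survival models".

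**Entry and follow-up.** The Population section excludes patients with BPSD but makes an exception for mild disturbance of mood, sleep or eating, mild anxiety and mild apathy. BPSD are recorded at baseline and at 6, 12 and 18 months.

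**The concern.** The objective is prospective: atrophy is measured at inclusion, and the question is who goes on to develop BPSD. The analysis named for it correlates atrophy with a BPSD label and does not say when that label is taken.

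Two things are at stake. First, a patient who enters with mild apathy and one who becomes apathetic at month 12 could carry the same label. The map would then show correlates of having a symptom at any time, not of developing it. Second, even with a clean label, the standard voxelwise model does not return a risk. The MRI result could not be set beside the odds or hazard ratios for social cognition, and it gives no stated route for atrophy to enter the combined risk assessment that the Discussion looks forward to.

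**Working it through.** The plan gives no figure for this point, so the main check sets the texts side by side.

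| Element | Social cognition | MRI |
|---|---|---|
| Question (Secondary objectives) | Risk of developing BPSD | Risk of developing BPSD |
| When the predictor is measured | Inclusion | Inclusion |
| Outcome in the named analysis | Onset of BPSD | Type of BPSD, timing not stated |
| Named method | Logistic and survival models | SPM correlation |
| Result on a risk scale | Odds or hazard ratio | None |
| Follow-up time and censoring | Used in the survival model | Not used |

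The two objectives ask the same kind of question of a baseline predictor. They part only at the analysis.

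**What the voxelwise model estimates.** In standard SPM/VBM the grey-matter value at each voxel is the dependent variable and BPSD status is the regressor:

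- SPM direction: volume = a + d × BPSD, where d is a mean difference in volume.
- Risk direction: logit P(BPSD) = a + b × volume, where exp(b) is an odds ratio per unit of volume.

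**Simulation of the two directions.** The inputs are:

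- N = 210, the number in the Sample size section before the allowance for drop-out.
- A BPSD risk of 40% at average volume. The 40% is from the same section, which set it for the main objective and not for MRI.
- A log odds ratio of 0 or 0.4 per SD of volume. This is an assumption, and its sign is immaterial here.
- 2,000 runs per scenario, tested at the two-sided 5% level.

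| True log OR per SD | Rejection, volume on BPSD | Rejection, logistic BPSD on volume | Mean estimate, volume on BPSD | Mean estimate, logistic |
|---|---|---|---|---|
| 0 | 4.3% | 4.0% | 0.005 SD | log OR 0.005 |
| 0.4 | 78.9% | 78.3% | 0.38 SD | log OR 0.406, so OR = exp(0.406) = 1.50 |

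Both directions detect the association about equally often. Only the second gives a risk estimate. The simulation treats one volume with a correctly coded new-onset outcome. It does not model whole-brain multiplicity, time to onset or drop-out.

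**Mixing of prevalent and new symptoms.** The share of patients who enter with a permitted mild symptom is not given, so the size of this effect cannot be calculated. That it can happen follows from the entry criteria together with a BPSD label that has no stated time.

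**The case against.** The strongest reply is that other sentences may already cover MRI. Data analysis opens with "To assess each study objectives, univariate and then multivariate analyses will be done to take into account potential confusion factors". Its logistic sentence for NPI-Q and Apathy Inventory outcomes, and its sentence on survival models for occurrence over time, name no exposure. Table 1 puts atrophy in the same class as personality and social cognition. This stands in part: risk models for MRI are not excluded. Yet none of those sentences names MRI, no regional MRI predictor is defined, and the sentence that does name MRI prescribes something else.

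A second reply is that the objective is worded as a correlation or relationship, and that the article also aims to find the anatomical correlates of BPSD, which a map serves well. This too stands in part. It is a good reason to keep the map. But both wordings of the objective name risk, and the sister objective shows which models the authors use for that.

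A third reply is that the article is condensed. That excuses missing detail such as region lists. It does not settle a named method that fits only part of the stated question.

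Three stronger readings are tempting, and the documents do not support them:

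- **That the objective goes unanswered.** SPM with a new-onset label does test whether baseline atrophy differs between patients who do and do not develop BPSD, at about the same power in the simulation. Onset is seen only at three visits, so the timing information is coarse in any case.
- **That drop-out biases the maps.** The Sample size section expects 42 drop-outs (252 − 42 = 210). Nothing says that they would be counted as free of BPSD. Leaving them out biases the maps only if loss is related to both atrophy and BPSD, and the article gives no information on that.
- **That VBM measures density when the objective is about atrophy.** The same sentence of the MRI section also says that brain volumes will be analysed.

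**Conclusion.** The point holds as a mismatch between a secondary objective and its named analysis. The MRI-specific analysis is not tied to new-onset BPSD, gives no odds or hazard ratio, and does not use follow-up time or censoring. The objective is therefore answered in part: association can be tested, but risk is not estimated.

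No numerical bias is claimed. The near-equal power rests on the assumed log odds ratio of 0.4, a 40% risk and N = 210, with one volume and correct outcome coding. The concern about mixed symptoms rests on the entry criteria and on reading the MRI sentence as it stands. It would fall away if a fuller plan already defines the label as new onset. The main objective is not affected. This is a worthwhile and inexpensive improvement, not a fault that threatens the study.

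**What to change.** 1. State that BPSD in the SPM analysis means new onset after the baseline visit, symptom by symptom. Say how a mild symptom already present at entry is treated if it persists or worsens. Name the score used in the VBM correlation.
2. In addition, extract one grey-matter volume per patient, adjusted for intracranial volume, for a few regions that the Background and Discussion already name, for example orbito-frontal or frontal cortex, medial temporal cortex and amygdala. Enter these as baseline predictors in the logistic and survival models already planned for social cognition, and censor drop-outs at their last visit in the survival models.
3. Keep the whole-brain SPM map alongside these models.

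The cost is revised analysis wording and some extraction and modelling work on scans and segmentations already planned. No new scans, visits or patients are needed. The drawback is that regional averages may blur a small focal effect, which the retained map covers. Regions not named in advance stay exploratory.

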## Discussion

The PACO study aims to better understand the factors underlying neuropsychiatric symptoms in patient with baseline prodromal or mild AD. This prospective multidisciplinary project brings together specialists in old age psychiatry, geriatric and neurology. Its main objective is to evaluate the effect of premorbid personality on the phenomenology and the frequency of BPSD. Premorbid personality will be assessed with the Five Factors Model, which is considered as the most widely used dimensional personality approach [53].

Several studies suggest that personality may influence the behavioral course of AD [19]. It has been yielded that persons with high neuroticism experience have more behavioral disturbances when measured with NPI [18]. The association between personality and specific neuropsychiatric symptoms is so far not fully established and should be better specified. For instance, high levels of neuroticism have been sometimes linked to depression [54] or not [18]. Most studies in this field are retrospective and include few patients, often in advanced stages of the disease. It can induce a substantial risk of recall bias, especially when personality is assessed by informants. The longitudinal design of PACO project, including more than 250 AD patients at prodromal or mild stage, can control some of these biases. Self-report of personality has been preferred to observer rating. In healthy people, this methodology is considered to be more accurate and trustworthy because observers do not have access to a person’s internal motives [55]. In the context of cognitive decline, self-assessment of personality could be criticized. However, Archer et al. showed that the NEO-FFI, a personality questionnaire based on the Big Five Inventory, can be used reliably to measure premorbid personality in AD patients [56]. Moreover, it has been shown that when asked to evaluate their current personality, persons with mild AD tended to describe their former personality [57], maybe due to an inability to update their self-image [58].

In PACO study, we are expecting to find correlations between personality dimensions and the risk of being affected by BPSD. We hypothesize that high level of neuroticism and low level of conscientiousness will be more specifically associated with BPSD, in particular affective domains such as depression, anxiety and apathy. As cognitive decline could be positively or negatively influenced by personality, this potential association will be studied [59, 60]. Moreover, as personality development is considered to be influenced by environmental factors, childhood and adult life events will be collected to assess their possible influence on the course of AD. This would allow us, for example, to highlight the possible effects of previous exposure to a trauma or childhood deficiencies.

Subjects included in PACO study will perform a comprehensive social cognition battery including facial emotion recognition tasks. Several publications have highlighted that AD patients experience an increasing deficit in facial emotional expression recognition as the disease progresses [23], but little is known concerning the very early stage of AD [61]. Consequences of impaired facial emotion recognition on behavioral troubles in AD are questioned and should be clarified [62]. Thus, a secondary objective of the PACO study is to compare social cognition ability between MCI and mild AD, and to identify potential relationships between social cognition abilities and BPSD occurrence during the patient’s follow-up.

PACO project includes MRI 3D sequence at baseline. Different studies have linked impaired emotion recognition in psychiatric or neurologic disease to disturbances or damages of the fronto-temporal brain network [63–65]. Social cognition parameters could be correlated to initial regional cerebral volume and/or the atrophy observed one year later, which could itself be correlated to a higher risk of developing BPSD. For instance, some orbito-frontal atrophy may predict the occurrence of BPSD. Recent evidence suggests that personality traits may be related to neuroanatomical structures. Jackson et al. [66] found that higher neuroticism was associated with specific brain regions atrophy, whereas higher conscientiousness was related to larger regional volumes in healthy aging. It could be hypothesised that an interaction between personality dimension, regional brain atrophy, and BPSD may exist in AD.

The PACO study may have several limitations. Firstly, personality should ideally have been assessed before AD onset. However, it would have been necessary to include a very large number of patients with a long follow-up. We have chosen to include patients at early stage of AD: at this stage we can suppose that the personality assessment reflects premorbid personality. Secondly, a longer follow-up would allow us to detect a larger number of BDSP. The absence of long-term follow-up could underestimate the relationship between personality and BDSP. Indeed, a certain number of SCPD increase with the evolution of the disease, but we hypothesized that some of them occur early in patients with specific personality traits. Thirdly, at baseline only patients with no or mild behavioural disturbances are selected. This inclusion methodology excludes subjects with personality dimensions associated to early behaviour disorder. Finally, the AD diagnosis was based on clinical and MRI criteria. Dubois et al. criteria refer to both imaging and to CSF markers [67]. This would allow better patient selection. However, in our centres, CSF markers are available for a small percentage of the patients, in particular when the diagnosis remains unclear. On the opposite, patients included in the PACO study had a typical clinical presentation, and CSF markers were not available for the majority of them. A systematic lumbar puncture should have limited the feasibility of our study.

The present study also has strengths. In most former studies personality assessment was performed by relatives and only a few included patients at prodromal or mild stage of AD. Moreover, to our knowledge, PACO is the first study to evaluate personality and social cognition performance and their link with subsequent BDSP.

The results of this research may help clinicians to better indentify, from a combined assessment of personality, performance in social cognition tests and the degree of cerebral atrophy, patients with AD at enhanced risk of developing BPSD and to improve patient and family care. Demonstrating a link between premorbid personality and behavioural problems will also allow us to argue for a veritable cooperation between neurologists, geriatricians and psychiatrists in the patients care throughout the course of the disease.

This study also aims to better understand the repercussions of early stage AD on social behaviour, identify the neuroanatomical correlates of BPSD. It should allow us to set up a regional data base to include clinical, neuropsychological, psychiatric, neuroradiological and biological data with longitudinal follow-up of the cohort, and then further inter-regional and inter-speciality cooperation in studying and dealing with Alzheimer’s disease.

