Overall, the methodology used in the previous studies makes interpreting results difficult, particularly as most studies are retrospective and include only a small number of patients, often with late stage AD. Such parameters can lead to bias in a patient’s self-evaluation since cognitive decline invariably leads to modification in the ability to express one’s own personality. A second area of bias comes from collecting data retrospectively from relatives. This implies subjective judgements, in an effort to preserve the image of the loved one, it is easy for family to minimise their BPSD or on the contrary to overestimate these behavioural problems and their effects on the family.

Social cognition is a cognitive domain involved in the detection and the recognition of social and emotional messages, as well as integration in a personal emotional context and a social complex context. It concerns one of the major aspects of our cognitive functioning allowing us to interact with our environment. A key component of social cognition is the ability to recognize facial emotion expressions, to identify and to judge mental state and the intentions of the others. It has been shown that impairment in the ability to recognise facial expressions is correlated to social behaviour in various psychiatric and neurological pathologies [21, 22]. Recent work has already shown that patients with AD also had impaired ability to recognise facial expressions [23]. Thus, impairment of social cognition ability in AD could influence the onset and the course of BPSD. Moreover, performance in social cognition tests like facial recognition and perspective taking could be linked to certain personality traits and the subsequent risk of BPSD.

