Furthermore, imaging markers could help to understand the link between brain structures changes and the presence of BPSD. The neuropsychiatric symptoms observed in AD patients could be mainly due to frontal structural abnormalities [24]. More specific regional associations with a range of behavioural symptoms have been identified: apathy was associated with frontal structures [25]; delusions were correlated with frontal, parietal, and temporal structures [26]; depressive symptoms with thalamus, lentiform nucleus, and medial temporal cortex [27]; agitation was associated with temporal and frontal structures [28] and amygdale atrophy was related to aberrant motor behaviour, with potential relationships to anxiety and irritability [29]. These same regions participate in the recognition of social messages, particularly those of facial expression, perspective taking and empathy [30]. Consequently, measurement of MRI markers may allow us to better understand the link between personality, social cognition and BDSP and the implication of the anatomic structures in these different domains.

We propose to assess personality in patients with prodromal or mild AD, and then to collect BPSD data prospectively with the objective to evaluate the causality link between personality and BPSD occurrence. Social cognition performance and cortical atrophy will also be measured at baseline.

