### Study aim and research question

#### A. Main objective

– To measure the effect of premorbid personality and life events on the likelihood of a patient with probable Alzheimer’s disease on the risk of developing BDSP.

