### Population

*Inclusion criteria are*: diagnostic criteria for AD at mild dementia stage, (NINCDS ADRDA and CDR 1) [31] or prodromal AD (CDR of 0.5) [32], age over 50 years, ability to complete the clinical and neuropsychological evaluations, and presence of a caregiver in sufficient contact with the subject to be able to note the onset of changes in behaviour.

*Exclusion criteria include*: patients with SCPD except from depression, anxiety, apathy, eating or sleep disorders at mild stage, patients with a progressive and/or poorly managed psychiatric pathology (patients with stabilised depression could be included in the study), patients taking *any* neuroleptic psychotropic medication, patients taking other psychotropic medication, with the exception of any antidepressant, hypnotic, anxiolytic, acetylcholinesterase inhibitors or Memantine which has been prescribed and stabilised for more than 3 months, and patients with serious, progressive or unstable pathologies which could interfere with the variables under consideration.

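### Nothing in the stated plan separates baseline depression, anxiety or apathy from the effect attributed to premorbid personality

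*Protocol article*

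**What the plan says.** All references are to the protocol article.

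- **Exposure and aim.** The main objective is "To measure the effect of premorbid personality and life events" on the risk of BPSD. The Background adds a causal aim, "with the objective to evaluate the causality link between personality and BPSD occurrence". Sample size rests on a relative risk tied to premorbid personality.
- **Measurement.** Personality is assessed at baseline, at CDR 0.5 or CDR 1. The Personality section uses two instruments: the NEO PI-R questionnaire, and a SCID II semi-structured interview whose diagnoses are confirmed collegially. The Discussion states: "Self-report of personality has been preferred to observer rating".
- **Eligibility.** The Population section excludes "patients with SCPD except from depression, anxiety, apathy, eating or sleep disorders at mild stage", so those mild symptoms are allowed at entry. Stabilised depression is also allowed.
- **Hypothesis.** The Discussion expects high neuroticism and low conscientiousness to go with BPSD, "in particular affective domains such as depression, anxiety and apathy".
- **Limitation and defence.** The Discussion concedes the timing: "Firstly, personality should ideally have been assessed before AD onset". It then says "at this stage we can suppose that the personality assessment reflects premorbid personality". It also cites one study on the reliability of the NEO-FFI for premorbid personality in Alzheimer's disease, and one finding that patients with mild disease tend to describe the person they used to be.
- **Analysis.** Data analysis plans multivariate models for confounders, without naming covariates. Table 1 lists demographics, diagnosis (including CDR) and psychotropic drugs as control variables. It lists GDS, like personality, as an influencing factor.

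**The concern.** The symptoms that may be present when the NEO PI-R is completed are the symptoms that the trait is expected to predict. Current low mood or anxiety can plausibly push a self-rated neuroticism score up. The same mood can also predict later depression, anxiety or apathy. The two links together produce an association between trait and outcome without any contribution from personality before the disease.

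Counting only new BPSD as events would not remove the problem, because the distortion lies in the exposure. If the models leave baseline mood out, part of a reported personality effect could be early affective BPSD predicting later affective BPSD. The declared limitations cover timing, length of follow-up, selection on baseline behaviour and diagnostic criteria. They do not mention contamination by mood.

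**Working it through.** **1. The plan's own figure.** Inputs from Sample size: BPSD in 40%, RR 1.5, alpha 5%, power 90%, giving 210. Taking 40% as the unexposed risk, the exposed risk is 0.40 × 1.5 = 0.60. With equal groups,

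n per group = [z_α·√(2·p̄(1−p̄)) + z_β·√(p0q0 + p1q1)]² / (p1−p0)²

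One-sided: [1.645 × 0.7071 + 1.282 × 0.6928]² / 0.04 = 105.2, so 106 per group and 212 in total, close to 210. Two-sided, the total is 260. The side of the test is a separate matter; here the figure only sets RR 1.5 as the yardstick.

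**2. Spurious RR with no trait effect (binary form).** The document gives no figure for the mood–trait or mood–BPSD link, so these inputs are assumptions:

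- share m with baseline affective symptoms: 20–50%
- high trait score in q1 = 60–70% of those with symptoms and q0 = 30–40% of those without
- RR of later BPSD for symptoms, r: 1.5–3
- overall BPSD risk 40%, from the document

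Formulas:

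- b0 = 0.40 / (m·r + 1 − m); b1 = r·b0
- risk if high trait = [m·q1·b1 + (1−m)·q0·b0] / [m·q1 + (1−m)·q0]
- risk if low trait: the same with 1−q1 and 1−q0

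| m | q1 / q0 | r | b0 | b1 | Risk, high | Risk, low | Spurious RR | Two-sided 5% rejection, n = 210 |
|---|---|---|---|---|---|---|---|---|
| 0.2 | 0.6 / 0.4 | 1.5 | 0.364 | 0.545 | 0.413 | 0.390 | 1.06 | about 5% |
| 0.3 | 0.7 / 0.4 | 2.0 | 0.308 | 0.615 | 0.440 | 0.362 | 1.21 | 21% |
| 0.4 | 0.7 / 0.3 | 3.0 | 0.222 | 0.667 | 0.493 | 0.321 | 1.54 | 72% |

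The first and last rows are the extremes of the grid. Within each mood stratum the RR is 1 by construction, so stratifying on true mood removes the whole effect.

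**3. Continuous form.** Assume mood explains 10–30% of the variance in the neuroticism score, with a mood odds ratio of 1.5–2.0 per SD, mean risk 40% and no trait effect. Comparing the upper with the lower half of the score then gives a spurious RR of 1.13–1.40.

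**4. What adjustment does.** Logistic regression, n = 210, 1,000 simulated studies per setting, trait–mood correlation 0.20–0.51, mood odds ratio 1.3–2.0 per SD, no trait effect:

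| Model | False rejection, two-sided 5% |
|---|---|
| Trait alone | 8–62% (spurious trait OR 1.05–1.39 per SD) |
| Trait + true mood | 4–6% |
| Trait + mood score of reliability about 0.7 | 6–11% |

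Simulation error is at most about √(0.62 × 0.38 / 1000) = 1.5 percentage points.

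**5. Precision of the subsets.** Two-sided power for 40% v 60% with n per group is Φ{[0.2·√n − 1.960 × 0.7071] / 0.6928}. All 210 (n = 105): 83%. If 20% have baseline symptoms, 168 remain (n = 84): 74%. If 50% do, 105 remain (n = 52.5): 54%. A CDR 0.5 stratum holding half of 210, a split the document does not give, would also have 54%.

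**The case against.** The strongest reply is that the article has already faced this. It declares the timing limitation and gives a feasibility reason. It offers two cited supports for self-report, enrols early to limit distortion, admits only mild symptoms, measures GDS and plans adjustment for confounders. Covariate lists commonly sit in the full protocol or analysis plan.

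Much of that stands, and it rules out several stronger readings that a reader might infer:

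- **That the premorbid label is bare supposition.** It is not; two supports are cited. But one concerns the NEO-FFI rather than the NEO PI-R, and neither is described as addressing current mood.
- **That the article contradicts itself** because the Background says that "cognitive decline invariably leads to modification in the ability to express" one's own personality. That sentence criticises previous studies, often in late-stage disease. Early enrolment is the authors' answer to it.
- **That all personality data are self-rated.** SCID II is a clinician interview with collegial confirmation. The concern falls mainly on the NEO PI-R, the source of the neuroticism score.
- **That GDS is left out of the models.** Table 1 does not say so. An influencing factor may enter a multivariable model, and CDR is already a control variable.

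What remains is that mood contamination appears neither in the limitations nor in the stated roles of the variables.

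**Conclusion.** The concern holds in a limited form. The exposure is named premorbid, is self-rated after onset on the NEO PI-R, and may be rated while the patient has the symptoms it is expected to predict. No stated step separates the two.

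The size is uncertain. With no true trait effect, the unadjusted spurious RR runs from about 1.06, which is negligible, to about the 1.5 the study is sized for. All inputs except the 40% risk are assumptions, and restriction to mild symptoms may favour the lower end. The upper end does not show that the study will mislead.

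Nor does it follow that a positive result could never be told apart from baseline mood. In the simulations, adjustment brought false rejection down to 4–6%, or 6–11% with an imperfect mood score, and the measures needed are collected. Adjustment cannot, however, prove that the trait is premorbid.

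**What to change.** 1. Report each model of NEO PI-R and BPSD twice: without, and with, baseline GDS, the baseline NPI-Q depression and anxiety items and the Apathy Inventory. GDS alone covers only depression.
2. As a sensitivity analysis, repeat the model in patients with no depression, anxiety or apathy at baseline.
3. Show the estimate for CDR 0.5 and CDR 1 descriptively.
4. In the conclusion, call the exposure personality self-rated at early-stage Alzheimer's disease. Discuss a premorbid interpretation according to how far the estimates agree.

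The cost is extra model runs on existing data. Adjustment may remove a true effect that runs through mood, which is why both estimates are needed. The symptom-free subset is less precise: 54–74% power under the assumptions above, against 83% for all 210.

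Two further steps are not advised. Asking patients to answer the questionnaire for the time before their illness adds recall burden and changes the measurement in a study already under way. Allowing the word premorbid only where an association persists after adjustment and in the CDR 0.5 stratum would make the wording depend on an underpowered subset and could discard a real effect.
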